##### Study blood

Platelets (determination of TSPO expression by Western blot), serum (creation of a neurosteroid profile using tandem mass spectrometry; cortisol (ELISA), whole blood (genotyping regarding the TSPO gene polymorphism rs6971).

#### Cortisol awakening response

To determine the cortisol awakening response (CAR) [45] saliva samples are taken from the patients using salivettes (chewing on cellulose rolls) (Sarstedt AG & Co., Nümbrecht, Germany) directly as well as 30 and 60 min after waking up. The saliva samples are stored for a short time at room temperature and in a freezer at – 20 °C until biochemical analysis.

#### Microbiome composition

To determine the bacterial composition of the human microbiome in depressive patients and its changes during the add-on treatment with etifoxine or placebo, stool samples from the patients will be analyzed. The complete genome will be sequenced using DNA. For this purpose, a stool sample is preserved in a sample container suitable for microbiome analysis and deep-frozen at – 80 °C for later analysis of the composition of the colon microbiome.

### Participant timeline {13}

#### Screening (D-1)

If participation is desired after the informed consent discussion, an appointment for the screening is made, which should take place maximum 1 week after the discussion.

After checking the dated signature of the patient information, the screening is started with the first blood sample (screening blood) and the urine sample for drug screening. For Women of Childbearing Potential (WOCBP), an additional pregnancy test will be carried out by assessing ß-HCG level in screening blood. A detailed psychiatric and somatic anamnesis is taken from all patients to rule out any mental comorbidities and physical illnesses. The Mini-International Neuropsychiatric Interview (M.I.N.I.) [32] will be used. In addition, an orienting general physical and special neurological examination is carried out as well as the measurement of blood pressure/pulse and ECG and the recording of body weight/height and body temperature. Furthermore, all other inclusion/exclusion criteria, concomitant diseases, and the use of stimulants are assessed.

#### Baseline (D0)

On the baseline day, the patients are asked to collect saliva samples using salivettes immediately and 30 and 60 min after waking up to determine the cortisol awakening response (CAR). Study blood and stool samples are also taken in the morning. In addition, vital signs such as weight are measured. Further, the self-evaluation questionnaires are handed out to the patients for completion and the external assessment ratings are carried out. The first measurement with the CANTAB test battery and the ARENA task also take place on this day. These two experimental paradigms can also be carried out on screening day T-1 after all inclusion/exclusion criteria have been checked. In the afternoon, the MRI session will take place at the research MRI scanner on the clinic premises.

#### Days 1 to 8 of treatment (D1 to D8)

Drug treatment begins one day after the baseline. From day 1 of treatment, patients receive the randomly assigned medication (etifoxine or placebo) daily from the nursing staff of the respective ward. The study medication should be taken at 8:00 am and 6:00 pm. On days 1 to 8 of treatment, the HAMD-21 and the MADRS are carried out daily with the patients, and the PHQ-9 and the VAS are given for completion. Possible AEs are recorded on days 1, 8, 15, 22, and 29. On day 8 of treatment, all other self-assessment and external assessment instruments are presented again.

#### Days 9 to 14 of treatment (D9 to 14)

Only the study medication is taken on these days. No examinations are carried out. AEs are not specifically queried but are recorded if they occur.

#### Day 15 after baseline (D15)

On day 15 after the start of treatment patients provide further saliva samples to determine the CAR. Also in the morning, the safety and study blood samples are taken, and the stool sample should be delivered. In addition, vital signs such as weight are determined. Blood pressure/pulse, ECG, and body temperature are also measured. The self-assessment questionnaires are presented to the patients for completion and the external assessment ratings are carried out. Afterwards, the second measurement with the CANTAB test battery and the ARENA method takes place. In the afternoon, the second MRI session is conducted.

#### Day 22 after baseline (D22)

On day 22, after the start of treatment, patients are asked to complete the self-assessment questionnaires, and the external assessment ratings are carried out.

#### Day 29 after baseline (D29)

At the final visit on day 29 after the start of treatment, the safety and study blood samples are taken, and the stool sample is submitted. In addition, vital signs are measured, and a physical examination is carried out. Patients are given the self-assessment questionnaires and the external assessment ratings are carried out. In the afternoon, the last MRI session takes place.

An overview of the study plan including all measures on safety as well as efficacy is given as a schedule of activities in Table 1.

**Table 1 Tab1:** Schedule of activities

Study day	D − 1	D0	D1	D2	D3	D4	D5	T6	D7	D8	D14	D15	D22	D29
	Screening	Baseline	Treatment phase									Follow-up		
Screening/safety blood	X											X		X
Drug screening urine	X													
Pregnancy test	X^A^													
Medical history	X													
MINI	X													
Physical/neurological examination	X													X
Vital parameters	X											X		X
Body weight	X											X		X
Concomitant medication/(concomitant diseases)	X											X		
HAMD-21, PHQ-9, VAS, MADRS		X	X	X	X	X	X	X	X	X		X	X	X
HAM-A, C-SSRS, BDI, SSS, BHWSS, BENDEP-SRW		X								X		X	X	X
Study medication			X^B^									X^C^		
Assessment of adverse events			X							X		X	X	X
Study blood		X										X		X
CANTAB, ARENA^D^		X										X		
fMRI		X										X		X
Cortisol Awakening Response		X										X		
Microbiome		X										X		X

^A^For WOCBP

^B^200 mg/day etifoxine or placebo

^C^Treatment according to clinical judgment

^D^These two experimental paradigms can also be performed on D-1 after checking all inclusion/exclusion criteria

### Sample size {14}

The calculation of the sensitivity of the planned analyses is based on recent work, which investigated the effects of treatment with SAGE-271 (zuranolone) compared to placebo in patients with the depressive disorder [30]. We used least squares approximation to estimate the parameters of an Emax model [46] considering the scores of the HAMD-21 reported by Gunduz-Bruce and colleagues. This resulted in Emax TAU + PLC = 0.586 and ET50 TAU + PLC = 4.224. This means that comparable TAU with an additional placebo would lead to a reduction of the HAMD-21 scores of 58.6% and that half of this decrease would be reached after slightly more than four days.

Montecarlo simulations of an Emax model based on the mentioned parameter estimations for TAU and on the reported standard deviation of the HAMD-21 scores with s = 2.6 in the study of Gunduz-Bruce et al. [30] show that a sample size of 20 patients per group (TAU + placebo, TAU + etifoxine) is sufficient to detect chances of therapeutic efficacy (Emax) of about 5% and changes of the response latency (ET50) of about 10% with a statistical power of 70%. Assuming a drop-out rate of 10–20% we plan to recruit in total of 50 patients (25 per group).

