**Methods:**

This is a randomized, placebo-controlled, double-blind single-center trial of 2-week treatment with the TSPO ligand etifoxine versus placebo in depressive patients. Main eligibility criteria: male or female individuals aged 18 to 65 years with unipolar/bipolar depressive disorder with no other psychiatric main diagnosis or acute neurological/somatic disorder or drug/alcohol dependence during their lifetime.

The primary endpoint is the time point at which 50% of the maximal effect has occurred (ET50) estimated by the scores of the Hamilton Depression Scale (HAMD-21). A total of 20 patients per group are needed to detect changes of therapeutic efficacy about 5% and changes of ET50 about 10% with a power of 70%. Assuming a drop-out rate of 10–20%, 50 patients will be randomized in total. The study will be conducted at the Department of Psychiatry and Psychotherapy of the University of Regensburg.

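### The stated 70% power for a 10% change in ET50 and a 5% change in Emax with 20 patients per group cannot be reproduced from the plan's own inputs; for ET50 it comes out at roughly 6–14%

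*Protocol article*

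**What the plan says.** Section {14} (Sample size) fits an Emax curve to published zuranolone data and takes the control values from it: "This resulted in Emax TAU + PLC = 0.586 and ET50 TAU + PLC = 4.224". It then describes Monte Carlo simulations based on these values and "on the reported standard deviation of the HAMD-21 scores with s = 2.6". From them it concludes that 20 patients per group "is sufficient to detect chances of therapeutic efficacy (Emax) of about 5% and changes of the response latency (ET50) of about 10" per cent, at a power of 70%. The abstract (Methods) restates this as the number of patients "needed to detect changes of therapeutic efficacy about 5% and changes of ET50 about 10% with a power of 70" per cent.

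Section {20a} fixes the analysis: for each patient, a Nelder-Mead least-squares fit with Emax and ET50 both free, then a t-test on each parameter. Section {18a} lists HAMD-21 ratings at baseline and on days 1–8, 15, 22 and 29. The primary objective and the Discussion speak of ratings up to day 15.

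**The concern.** ET50 is the primary endpoint, and this sentence is the only justification given for 20 per group. A 10% change in ET50 is 0.42 days. A quick look at the curve shows how little that is on the rating scale. At an assumed baseline of 25, the two mean curves are furthest apart near day 4, by 25 × 0.586 × (4/7.8016 − 4/8.224) = 0.39 HAMD-21 points. With an SD of 2.6 and 20 per group, the standard error of a group difference at a single visit is 2.6 × √(2/20) = 0.82 points.

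ET50 is also hard to separate from Emax, because the plateau is not reached within the study. The control curve has covered 15/19.224 = 78% of Emax by day 15 and 29/33.224 = 87% by day 29.

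If the stated sensitivity is wrong, a null result on ET50 could be taken as evidence against a 10% shift that the trial had little chance of detecting.

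**Working it through.** **Inputs from the article.** Emax 0.586; ET50 4.224 days; s = 2.6; 20 per group; 1:1 allocation; two free parameters per patient; t-test; visits D0–D8, D15, D22, D29, or the same list ending at D15.

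**Assumptions, because the article does not state them.** s is independent error at each visit. Baseline B is 20, 25, 30 or 36 and known (the article gives only the entry threshold of above 18). Alpha is 5%, two-sided. There is no true variation between patients in Emax or ET50, which favours the plan.

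**The plan's own figures.** The dropout step reproduces: 40/(1 − 0.2) = 50. The 70% does not, as follows.

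**Step 1: what 70% power requires.** With 20 per group (38 df) and two-sided 5%, the noncentral t gives a standardised difference of 0.806. The SD of fitted ET50 across patients may then be at most 0.4224/0.806 = 0.52 days.

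**Step 2: what the design delivers.** The model is HAMD(t) = B·(1 − Emax·t/(t + ET50)). Write u = t/(t + ET50) and v = t/(t + ET50)², summed over visits. The linearised standard errors of one patient's estimates are

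- SE(ET50) = s/(B·Emax) · √[Σu² / (Σu²·Σv² − (Σuv)²)]
- SE(Emax) = s/B · √[Σv² / (Σu²·Σv² − (Σuv)²)]

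Control arm, visits to D29: Σu² = 4.079, Σuv = 0.2929, Σv² = 0.02687, so the bracketed difference is 0.02382. At B = 25, SE(ET50) = 2.6/14.65 × √(4.079/0.02382) = 2.32 days and SE(Emax) = 2.6/25 × √(0.02687/0.02382) = 0.110. The two estimates correlate at 0.88. To D15, SE(ET50) is 3.52 days and the correlation is 0.95.

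**Step 3: power for a 10% shortening of ET50.** Each arm has its own SE. At B = 25 to D29 these are 2.32 and 2.07 days, pooled √[(2.32² + 2.07²)/2] = 2.20. The noncentrality is 0.4224/(2.20 × √(2/20)) = 0.61, against a critical value of 2.02, which gives 9.1%.

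| Baseline | SE(ET50), control, D29 | Power, D29 | SE(ET50), control, D15 | Power, D15 |
|---|---|---|---|---|
| 20 | 2.90 | 7.6% | 4.40 | 6.1% |
| 25 | 2.32 | 9.1% | 3.52 | 6.8% |
| 30 | 1.94 | 11.0% | 2.94 | 7.6% |
| 36 | 1.61 | 13.7% | 2.45 | 8.8% |

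The best one-sided case (baseline 36, D29) is about 22%.

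**Step 4: Emax.** A relative 5% is 0.0293. At B = 25 to D29 the noncentrality is 0.0293/(0.110 × √(2/20)) = 0.84, giving 13%. Over baselines 20–36 and both windows the range is about 7–22%. If 5% means 0.05 absolute, it is about 9–52%.

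**Step 5: check by simulation.** Nelder-Mead fits at known baseline 25 gave about 8–10% to D29 and about 4–5% to D15. Using the observed D0 score as the baseline lowers ET50 power to about 4% in one run to D29. Runs with a noisy or fitted baseline ranged from about 1% to 7%, because unbounded fits produce extreme ET50 values. Adding between-patient variation (CV 30% for ET50, 20% for Emax) gave 6% at baseline 25 to D29.

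**Step 6: what 20 per group can detect.** Letting the SE shrink as ET50 shortens, 70% power is reached at these shortenings of ET50:

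| Baseline | To D29 | To D15 |
|---|---|---|
| 20 | 45% | 63% |
| 25 | 37% | 52% |
| 30 | 32% | 45% |

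These linearised figures are optimistic. At baseline 25 to D29 the simulated SD of fitted control-arm ET50 was about 2.8–2.9 days, against 2.32.

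**The case against.** The strongest reply is that the article condenses a fuller protocol. Mean baseline, alpha, sidedness and the error structure of the simulation are not given, and the 2.6 comes from a publication not at hand. That is fair, and the absence of those items is not itself an error. It does mean that my figures rest on assumptions. But varying the assumptions does not rescue the claim. A one-sided test, which would fit the directional primary question, stays at or below about 22%. Log ET50, a rank test and bounded fits stay near the same level. Freeing only ET50, contrary to {20a}, gives 15–32%.

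Values near 70% appear only under readings that the text does not support. Taking s as 2.6% of baseline gives 66% for ET50 but 89% for Emax. Dividing s by √20 gives 76% and 97%. If s were purely spread between patients with no visit error, each patient's ET50 would be recovered exactly and power would be near 100%.

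Two stronger readings are tempting and do not hold. A reader might infer that the trial could miss even a halving of ET50. With all visits, power for a halving is about 81% at baseline 20 and 94% at 25. Only the window to D15 leaves it in doubt (48%, 67% and 82% at baselines 20, 25 and 30). A reader might also carry the control arm's SE into both arms and get a detectable change of 0.806 × 2.32/4.224 = 44% at baseline 25 to D29. That overstates the requirement, because the SE falls as ET50 shortens; the arm-specific figure is 37%.

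Finally, the article calls the trial a first proof-of-concept. Modest sensitivity is acceptable in such a trial, but that does not make the printed power figure correct.

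**Conclusion.** The power statement is wrong as written. From the plan's own Emax, ET50, SD, visits and analysis, two-sided power for a 10% change in ET50 is about 8–14% (to D29) or 6–9% (to D15), against a stated 70%. The Emax part fails too, on either meaning of 5%. To give 70% for ET50 at baseline 25 with all visits, the visit SD would have to be about 2.6 × 0.52/2.32 ≈ 0.6 points.

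The exact values depend on the assumed baseline, alpha, independent visit error and absence of between-patient variation. The conclusion does not change over the ranges tried, and true between-patient variation would lower power further. The documents do not show that the trial is insensitive to large effects, or that 50 patients is the wrong number for a proof-of-concept trial.

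**What to change.** Re-run the Monte Carlo simulation with the exact planned fit and t-test, the visit window that the primary analysis will use, and visit-level error of 2.6. State the baseline, how the baseline enters the fit, the between-patient variation, alpha and sidedness. Then replace the 5%/10%/70% statement in {14} and in the abstract with the detectable change from that simulation. The detectable-change figures above are a guide to the order of magnitude and should not be printed in its place.

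The sample of 50 and the analysis can stay. The cost is one simulation run and a text correction in two places. The downside is that the stated sensitivity becomes less favourable.

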### Recruitment {15}

We closely communicate with the central occupancy management of the hospital to be pre-informed about potential candidates and to not miss any admission throughout all the wards. Furthermore, we directly informed resident psychiatrists in the surroundings about the trial, placed advertisements with study information on the hospital homepage, and distributed leaflets at relevant locations.

## Assignment of interventions: allocation

### Sequence generation {16a}

The randomization list was set up blockwise by a biometrician of the Center for Clinical Studies, University of Regensburg, using the software SAS 9.4. Patients will be randomly assigned to receive either etifoxine or placebo with an allocation ratio of 1:1.

### Concealment mechanism {16b}

The randomization list was directly sent to the pharmacy of the University Hospital of Erlangen, which is responsible for the production of the study medication as well as the respective documents. This list will not be accessible for any member of the study team during the duration of the trial.

The investigational product and placebo will be repackaged and blinded by the pharmacy of the University Hospital of Erlangen to ensure that the compounds are identical with respect to appearance, packaging, and lablling. All patients receive the same number of capsules.

### Implementation {16c}

All patients who give their informed consent for participation in the trial and who fulfil the inclusion criteria will be randomized. Patients will be randomized in a sequential manner following the order of their inclusion.

## Assignment of interventions: blinding

### Who will be blinded {17a}

The study medication will be administered in a double-blind manner. This means that neither patients nor any member of the study team knows which treatment arm the patients are allocated to. All statistical analyses will be conducted under maintenance of the blinding.

### Procedure for unblinding if needed {17b}

Emergency envelopes for unblinding prepared by the pharmacy are kept locked in the research ward. In the event of an emergency, it is ensured that the trained ward staff has access to those envelopes at all times. In such a case, the sponsor must be informed on the next working day. A written justification will be submitted subsequently in this case. After unblinding, the clinical trial must be terminated for the respective patient.

## Data collection and management

### Plans for assessment and collection of outcomes {18a}

The primary outcome parameter is ET50 estimated using the Hamilton Depression Scale (HAMD-21) scores collected on baseline day and on days 1, 2, 3, 4, 5, 6, 7, 8, 15, 22, and 29 of treatment. To guarantee good quality of the assessment, we have designated a fixed team of raters that were internally trained by experienced psychiatrists with a focus on high inter-rater consistency. Additionally, all ratings for one patient will consistently be performed by the same rater. For a description of all other outcome parameters see {12}.

A web-based, electronic Case Report Form (eCRF) within a validated database management system is used for the database-supported recording of study data. This system enables consistent data storage and quality control. Qualified entry personnel are given access to the eCRF by assigning personal login data. A medical investigator confirms timely with an electronic signature that the study data was entered into the database completely and correctly.

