#### Primary objective

The primary objective of the trial is to investigate the effects of add-on treatment with etifoxine on clinical symptoms in patients with severe unipolar/bipolar depressive disorder. Clinical symptoms will be assessed using the Hamilton Depression Scale (HAMD-21) [31] up to day 15 after the start of the treatment.Does add-on treatment with the TSPO ligand etifoxine in addition to TAU for 14 days fasten the treatment response (decrease of ET50; ET50 = time point at which 50% of the maximal effect has occurred) in comparison to placebo?

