#### Secondary objectives

Does add-on treatment with etifoxine compared to placebo in addition to TAU in depressive patients lead to.A decrease of the Emax (= maximum effect which can be expected from the drug)?A reduction of the HAMD-21 score on day 15?Changes of the synthesis of neurosteroids, TSPO expression or activity of the hypothalamic–pituitary–adrenal axis?Changes in cognitive functions like memory or emotional processing assessed with a neuropsychological test battery?Changes of functional neuronal networks and cognitive functions assessed using fMRI applying resting state measurements and two tasks ((representational similarity analysis) RSA and face-name-association (FNA))?Changes of the microbiome composition?A relapse or withdrawal symptoms after discontinuation of the intake?

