### Trial design {8}

This is a single-center, randomized, parallel-group, placebo-controlled, double-blind investigator-initiated superiority clinical trial (IIT) with two arms. Eligible patients will receive either etifoxine or placebo for a period of 14 days. The patient allocation ratio is 1:1. Measurements will be taken up to 29 days after the start of the study treatment. The trial will be conducted with 50 patients suffering from unipolar/bipolar depressive disorder.

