## Statistical methods

### Statistical methods for primary and secondary outcomes {20a}

Statistical analyses will be conducted by the Center for Clinical Studies, University of Regensburg in collaboration with the Biomedical Imaging group of the Department of Psychiatry and Psychotherapy, University of Regensburg. We will use SAS (version 9.4 or higher), Matlab (version 2021a or higher), R (R Core Team, 2020), and scikit-learn (1.3.2 or higher) for the analyses.

Baseline characteristics and demographic data will be presented descriptively for all patients and separately for the two treatment groups. Categorical variables will be reported by absolute and relative frequencies, interval scaled data using descriptive values like mean, standard deviation, median, interquartile range, minimum, and maximum.

Primary endpoint: Using the Nelder-Mead Simplex method (implemented in Matlab) we will conduct a nonlinear minimization of the square deviation of the HAMD-21 scores from an Emax function with the free parameters Emax and ET50 for each patient. Emax and ET50 will be tested each per t-test for mean value differences between TAU + Placebo and TAU + Etifoxine.

Secondary endpoints: All secondary endpoints will be analyzed only exploratory and will be defined in detail in the Statistical Analysis Plan. There will be no multiplicity adjustments of the *p*-values.

Safety endpoints: All data concerning the safety of the investigational product will be listed and reported in comparison to placebo. All (serious) adverse events will be summarized in frequency tables and will further be reported separatly according to intensity and relation to the investigational product.

Imaging data will be analyzed using specialized software (FSL, http://fsl.fmrib.ox.ac.uk) and with own Matlab- and Python-based programs. In all conducted tests we make no assumptions on the distribution of the data and therefore use computer-based randomization tests for the evaluation of significance.

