## Discussion

We here describe the study protocol for a single-center, randomized, placebo-controlled clinical trial on the effects of the TSPO ligand etifoxine in the treatment of depressive disorders. The primary objective of the trial is to investigate the effects of add-on treatment with etifoxine on clinical symptoms in patients with severe unipolar/bipolar depressive disorder. Clinical symptoms will be assessed using the HAMD-21 up to day 15 after the start of the treatment.

In advance, we were aware of some challenges in conducting this trial, including mainly the recruitment of eligible patients and their continuance in the study. We have taken several precautions to address these challenges as we pointed out in sections {15} and {18b}. Overall, we try to realize inclusion to the trial close in time to inpatient admission to increase the chance that included patients stay at the hospital until the end of the trial 29 days after starting the study medication. In any case, the primary outcome is measured at a relatively early time point (2 weeks after the start of the study treatment). Overall, the study team has a good track record in enrolling and following participants in previous trials and there were no drop-outs of participants in former trials investigating the effects of etifoxine at the site [47–49].

The merit of this study is that it is the first proof-of-concept study on the TSPO ligand etifoxine in the treatment of depression, which may promote endogenous neurosteroid synthesis. With its favorable side effects profile, it could become a valuable compound, which might help in enhancing the effects of established antidepressant medication as an alternative to exogenously administered neurosteroids, e.g., zuranolone*.*

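### The primary ET50 is defined from HAMD-21 scores through days 22 and 29, after study drug has stopped, although the primary objective ends at day 15; any off-drug difference between the arms would distort it

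*Protocol article*

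**What the plan says.** In the protocol article, section {18a} names ET50 as the primary outcome parameter and says it is estimated from HAMD-21 scores "collected on baseline day and on days 1, 2, 3, 4, 5, 6, 7, 8, 15, 22, and 29 of treatment".

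Other sections set a shorter window:

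- The Primary objective assesses symptoms with the HAMD-21 "up to day 15 after the start of the treatment".
- The Discussion repeats day 15 and says that "the primary outcome is measured at a relatively early time point (2 weeks after the start of the study treatment").
- Trial design {8} says: "Eligible patients will receive either etifoxine or placebo for a period of 14 days". Table 1 heads day 15 onward as follow-up, and its footnote C reads "Treatment according to clinical judgment".
- The Secondary objectives ask separately about "A relapse or withdrawal symptoms after discontinuation of the intake".

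Section {20a} describes a "nonlinear minimization of the square deviation of the HAMD-21 scores from an Emax function with the free parameters Emax and ET50 for each patient". It then compares ET50 and Emax between arms, each by t-test. It does not say which visits enter the fit.

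**The concern.** Days 22 and 29 are called days of treatment, but they fall at least a week after the last dose. Two of the eleven post-baseline scores in the primary curve therefore describe patients who no longer take etifoxine or placebo and whose other care is not fixed by the protocol.

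The fitted curve cannot turn back. If a patient's improvement stalls or reverses after day 15, least squares can follow only by lowering the plateau (Emax). A lower plateau is half reached sooner, so ET50 falls. An event that the protocol treats as a possible harm, and as a separate question, would then enter the primary endpoint as speed of response.

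The comparison between arms is affected whenever the off-drug course differs between them. While two windows stand in the text, the choice between them could also be made after the data are seen.

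**Working it through.** **Inputs from Sample size {14}.** Emax 0.586 (fraction of baseline), ET50 4.224 days, HAMD-21 SD 2.6, 20 patients per group, target change in ET50 about 10%, that is 0.1 × 4.224 = 0.42 days.

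**Assumed, because the article gives no figure.** Baseline HAMD-21 of 25 (also 20 and 30), independent noise between visits, two-sided 5% level, and the size of any off-drug worsening.

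**Model.** Improvement as a fraction of baseline: f(t) = Emax × t / (ET50 + t), with f(0) = 0, fitted by least squares.

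**Step 1, unperturbed curve.** With baseline 25:

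- Day 15: 25 × 0.586 × 15 / 19.224 = 11.43 points.
- Day 22: 25 × 0.586 × 22 / 26.224 = 12.29 points.
- Day 29: 25 × 0.586 × 29 / 33.224 = 12.79 points.

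Without noise, the fit returns Emax 0.586 and ET50 4.224 whether it stops at day 15 or day 29.

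**Step 2, worsening at days 22 and 29 only.** Subtract w points from the curve at those two visits and refit. The on-drug course is unchanged.

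| w (points) | w as share of day-15 gain | ET50, fit to day 29 | Change | Emax, fit to day 29 | ET50, fit to day 15 |
|---|---|---|---|---|---|
| 0 | 0% | 4.22 | 0% | 0.586 | 4.22 |
| 1 | 9% | 3.53 | −16% | 0.540 | 4.22 |
| 2 | 17% | 2.95 | −30% | 0.500 | 4.22 |
| 4 | 35% | 2.05 | −51% | 0.434 | 4.22 |
| 6 | 52% | 1.43 | −66% | 0.382 | 4.22 |

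For 2, 4 and 6 points, ET50 is 2.69, 1.71 and 1.08 days with baseline 20, and 3.13, 2.31 and 1.71 days with baseline 30.

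The 1-point row is hardly a relapse: improvement would be 11.29 points at day 22 and 11.79 at day 29, against 11.43 at day 15. Holding improvement exactly at its day-15 level gives ET50 3.44 days, or −18%. Both shifts exceed the 10% target.

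**Step 3, direction.** What matters is the difference between arms.

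- Etifoxine 4 points worse, placebo 0: 2.05 against 4.22 days, so etifoxine looks faster.
- Placebo 4, etifoxine 2: 2.05 against 2.95 days, so etifoxine looks about 0.9 days slower.
- Both 4: 2.05 in each arm. There is no difference, although both values are about half the on-drug ET50.

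**Step 4, effect on the t-test.** Simulated trials with 20 per arm, SD 2.6, baseline 25 and no true difference in ET50:

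- No worsening: about 2–5% rejection, depending on how the fit is done.
- Etifoxine arm only, 2, 4 and 6 points: 46%, 95% and 100% with the baseline score treated as fixed, and about 10%, 35% and 61% with each curve anchored to a noisy baseline score.
- Equal worsening of 4 points: about 5%.
- Placebo 4, etifoxine 2: 44%, all against etifoxine (fixed baseline).
- Fit stopped at day 15: about 3–4%.

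**Step 5, precision lost by stopping at day 15.** The asymptotic covariance is s²(JᵀJ)⁻¹ with s = 2.6 / 25 = 0.104. The columns of J are t/(ET50 + t) and −Emax × t/(ET50 + t)². The per-patient standard error of ET50 is 2.32 days with visits to day 29 and 3.52 days with visits to day 15, a ratio of 1.52.

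**The case against.** **The day list may be only a collection schedule.** It sits in the data-collection section and matches the HAMD-21 row of Table 1. The objective and Discussion could then supply the analysis window, and an unseen analysis plan may state it. This has some force, but {18a} ties the listed days to how ET50 is estimated and {20a} sets no limit. The article as written still gives two windows.

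**The bias need not favour etifoxine.** This stands. A reader might infer that the plan is tilted towards the drug. The documents do not support that: they only ask whether relapse occurs, give no rate or direction, and provide usual treatment to both arms. Equal worsening largely cancels, and greater worsening after placebo works against etifoxine.

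**The larger scenarios are severe.** Six points is about half the day-15 gain, lost in every patient of one arm that had no on-drug benefit. This also stands, but the mechanism does not need such a case. If etifoxine raises Emax by 5 to 15 percentage points on drug with the same ET50, and scores then return to the placebo curve, the fitted ET50 is 16% to 37% shorter.

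**The rejection rates are not firm.** Agreed. They move from 10% to 46% for the same 2-point worsening according to how the baseline score is handled, which the article does not state.

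**The late visits help to identify the plateau.** True, and the loss of precision without them is real. The gain holds only if the off-drug scores follow the on-drug curve.

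**Conclusion.** The contradiction is on the page: {18a} builds the primary ET50 on off-drug scores, while the Primary objective and Discussion stop at day 15 or two weeks. Following {18a} can give a wrong primary result, because an Emax curve converts off-drug worsening into a shorter ET50. On the article's own curve with an assumed baseline of 25, 1 to 6 points of worsening move ET50 from 4.2 to between 3.5 and 1.4 days, and a fit to day 15 does not move at all.

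The between-arm bias requires different off-drug courses in the two arms and can run either way. False-positive inflation is possible, but its size rests on the assumed relapse and on how the per-patient fits are done, so no single rate should be quoted. Because Emax falls with ET50, a shorter ET50 could also accompany a worse outcome. The two windows need to be reconciled before unblinding.

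**What to change.** In {18a} and {20a}, define the primary ET50 and Emax from the HAMD-21 at baseline, days 1–8 and day 15 only, in line with the Primary objective, and stop calling days 22 and 29 days of treatment. Use those two visits for the relapse and withdrawal objective and for a sensitivity fit labelled as including off-drug scores.

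The change is one of wording and needs no new data. Its cost is precision: with SD 2.6 and baseline 25, the per-patient standard error of ET50 rises from about 2.3 to 3.5 days, and some individual fits become unstable because only days 8 and 15 lie late on the curve. The 70% power statement in {14} does not say which visits were simulated. It should be rerun and restated on the day-15 schedule, with the baseline, noise model and significance level given.
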